## Abstract

**Introduction:**

The prevalence of chronic, lifestyle-related diseases is increasing among adults and children from low-income and middle-income countries. Despite the effectiveness of community-based interventions to address this situation, the benefits thereof may disappear in the long term, due to a lack of maintenance, especially among disadvantaged and high-risk populations. The *KaziBantu* randomised controlled trial conducted in 2019 consisted of two school-based health interventions, *KaziKidz* and *KaziHealth*. This study will evaluate the long-term effectiveness and sustainability of these interventions in promoting positive lifestyle changes among children and educators in disadvantaged schools in Nelson Mandela Bay, South Africa, in the context of the COVID-19 pandemic.

**Methods and analysis:**

This study has an observational, longitudinal, mixed-methods design. It will follow up educators and children from the *KaziBantu* study. All 160 educators enrolled in *KaziHealth* will be invited to participate, while the study will focus on 361 *KaziKidz* children (aged 10–16 years) identified as having an increased risk for non-communicable diseases. Data collection will take place 1.5 and 2 years postintervention and includes quantitative and qualitative methods, such as anthropometric measurements, clinical assessments, questionnaires, interviews and focus group discussions. Analyses will encompass: prevalence of health parameters; descriptive frequencies of self-reported health behaviours and quality of life; the longitudinal association of these; extent of implementation; personal experiences with the programmes and an impact analysis based on the Reach, Efficacy, Adoption, Implementation, Maintenance framework.

**Discussion:**

In settings where resources are scarce, sustainable and effective prevention programmes are needed. The purpose of this protocol is to outline the design of a study to evaluate *KaziKidz* and *KaziHealth* under real-world conditions in terms of effectiveness, being long-lasting and becoming institutionalised. We hypothesise that a mixed-methods approach will increase understanding of the interventions’ capacity to lead to sustainable favourable health outcomes amid challenging environments, thereby generating evidence for policy.

**Trial registration number:**

ISRCTN15648510

Strengths and limitations of this studyThe cohort of children was purposely and objectively identified based on their high-risk profile; the follow-up of personal health outcomes is of additional value.The mixed-methods approach, strengthened by the involvement of the community and key stakeholders, will enable a comprehensive evaluation of the programmes.Internationally recognised measurement methods for quantitative, as well as qualitative, were selected and adapted to the study setting.The COVID-19 pandemic might influence schools’ decision to discontinue or adapt the post-*KaziBantu* intervention and the research team will assess, but not influence, its implementation.The study will yield context-specific results that will be closely linked to COVID-19 measures and practices adopted by the schools.

## Introduction

Socioeconomic, environmental and cultural factors exert a significant influence on children’s health and well-being.^1^ In impoverished communities in low-income and middle-income countries (LMICs), children are especially vulnerable to illness and lags in age-appropriate development, negatively affecting their life prospects.^2–4^ This precarious situation has been aggravated by the COVID-19 pandemic, which has compromised millions of South African children’s education, mental health and nutrition.^5^ Furthermore, the disease profile of urban populations from LMICs is approaching that of high-income countries, as the proportion of deaths attributable to chronic, lifestyle-related diseases increases.^6–8^ Of particular concerns are changing dietary habits and sedentary lifestyle patterns,^9 10^ both known to lead to metabolic and physiological changes, such as obesity and hypertension, also in young children.^11 12^ Children presenting with cardiometabolic risk factors are at particularly high risk because of their predisposition to developing non-communicable diseases (NCDs) later in life.^13 14^ Thus, a reduction of undesired behaviours could potentially prevent the majority of chronic diseases, indicating a great need for prevention programmes and awareness campaigns.^15 16^

Global recommendations for physical activity (PA) stipulate a daily minimum of 60 min of moderate-to-vigorous PA for children between 5 and 17 years old. Walter showed that the levels of in-school PA among children from marginalised communities in South Africa do not meet the minimal requirements,^17^ which was later confirmed by ‘The Healthy Active Kids South Africa Report Card’ (2018).^18^ Therefore, there is an urgent need to promote PA among at-risk communities in South Africa. Several school-based lifestyle interventions have proved effective in increasing levels of PA and reducing obesity in children from different contexts.^19–21^ However, very few school-based and large-scale PA intervention studies have been conducted in South Africa. The first study, *HealthKick*, was set in disadvantaged low-income communities in Cape Town and aimed at promoting healthy eating habits and regular participation in PA in children to reduce the risk of chronic diseases.^22^ Study results were not completely satisfactory and highlighted that educators play a key role in implementing lifestyle interventions in schools.^23 24^ Some studies have reported beneficial effects of integrated community-based interventions involving the participation of educators and children.^25–27^

‘Disease, Activity and Schoolchildren’s Health’ study documented the poor health status and double burden from communicable and NCDs of children in disadvantaged communities in Gqeberha, formerly known as Port Elizabeth, South Africa.^28^ It also revealed the potential for improvement through PA and health literacy interventions, following the principles that PA is key for the promotion of health and well-being among school children, and that learning this at a young age will have long-lasting effects throughout life. Moreover, it emphasised the role of educators as influential and willing advocates.^29^ Building on these results and experience, *KaziBantu*, a comprehensive school-based lifestyle intervention programme aiming at promoting health literacy in both children and educators of primary schools from disadvantaged communities in Nelson Mandela Bay (NMB) was developed.^30^*KaziBantu*, which is a composite Swahili and isiXhosa phrase meaning «Active People», was designed as a dual approach consisting of two school-based health promotion interventions, *KaziKidz* for children and *KaziHealth* for educators, and was implemented as a cluster randomised controlled trial (RCT) between January and October 2019. Preliminary results show that more than half of the assessed children (544/975) presented at least one risk factor for NCDs. Educators responded positively to the intervention as they felt the programme was also focused on their health and well-being (individualised results were communicated to the study participants) and took cognizance of the difficult work environment they faced daily.

Furthermore, evidence suggests that general and work-related stress increases the risk of mental ill health (burnout, anxiety, impaired quality of sleep), as well as physical disease (coronary heart disease and musculoskeletal disease). These factors seem to contribute to an increased risk of premature death.^31^ This risk was confirmed in a large representative sample of South African educators (N=21 307) working in public schools. High stress levels, lack of job satisfaction and different stress-related physical illnesses (hypertension, heart disease, stomach ulcers, mental distress, tobacco and alcohol misuse) were reported.^32^

Although evidence exists on the effectiveness of community-based lifestyle interventions in LMICs,^33^ studies have also shown that positive effects tend to disappear in the long term,^34^ sometimes because programmes fail to be maintained.^35 36^ In addition, there is still a scarcity of evidence regarding the feasibility of educational programmes in at-risk populations in disadvantaged school settings. We hypothesise that a comprehensive approach focusing specifically on high-risk children and their educators might increase implementation feasibility and ultimately lead to sustainable favourable health outcomes in both groups.

### Objectives

The goal of this follow-up study is to determine the long-term post-RCT effectiveness, adoption and continuity of both *KaziKidz* and *KaziHealth* school-based health interventions in disadvantaged primary schools in NMB, South Africa, under real-world conditions and amid the COVID-19 pandemic. To achieve this goal, the following objectives are set:

To assess the effectiveness of the interventions in promoting long-lasting, positive lifestyle changes among children and educators, thereby reducing risk factors for NCDs;To evaluate the postintervention sustainability concerning the continuation of the programme implementation in the schools as well as the institutionalisation within the Eastern Cape Department of Education (ECDoE) in South Africa.To provide recommendations towards guidelines for a health promotion framework, as well as its adaption to new contexts that may be translated into policy and practice.

## Methods

### Research setting

This study is conducted in the eight schools originally selected for the *KaziBantu* RCT.^30^ These are quintile three primary schools in the townships and Northern areas of NMB, in the Eastern Cape province of South Africa. The quintiles of South African schools are determined through the national poverty table and are ranged on a scale from 1 (poorest) to 5 (least poor). Quintile three schools represent no-fee paying schools and their communities are adversely affected by poverty and high unemployment rates.

### Study population

Originally, in the *KaziBantu* project, both *KaziKidz* and *KaziHealth* interventions were conducted in four schools, whereas the other four participating schools were used as controls.^30^ In total, 975 children from fourth to sixth grade (aged 8–16 years) were enrolled in the study; 482 children were allocated to the intervention and 493 to the control arm. At the same time, 160 educators were enrolled among all participating schools; of those, 85 took part in *KaziHealth,* whereas 75 served as waiting-list controls.

This study will follow up children and educators from the *KaziBantu* trial. While all educators who took part in *KaziHealth* have been invited to participate in this follow-up phase, a cohort of children from the *KaziKidz* intervention, who have been identified as having an increased risk for NCDs, have been included in this study. We have defined increased risk as a child presenting at least one of the following cardiometabolic risk factors: (1) overweight or obesity, (2) elevated blood pressure or hypertension, (3) pre-diabetes or diabetes, (4) borderline or dyslipidaemia; according to age appropriate, standard classifications (table 1) and based on *KaziBantu* baseline data from July 2019. Of the 975 children who participated in *KaziKidz*, 544 were classified as «high risk» according to the above-mentioned definition. Since then, 183 children have graduated from primary school resulting in 361 eligible learners. Of those, 240 have consented to participate and have been enrolled in this follow-up study at the time this protocol was published. Of the 160 educators enrolled in the *KaziHealth* program in 2019, 105 have consented to participate and have been enrolled in this study so far.

**Table 1 T1:** Classification criteria for cardiometabolic risk in children

Risk factor	Indicators and cut-off points
Adiposity^59 60^	BMI-for-age (SD)
Overweight	>+1 and ≤+2
Obesity	>+2
Blood pressure^61 62^	SBP and/or DBP (percentiles and mm Hg)
Elevated blood pressure	≥90th and <95th or <90th but ≥120/80
Hypertension stage 1	≥95th and ≤99th or ≥130/80
Hypertension stage 2	>99th or ≥140/90
Glycaemia^63^	HbA1c (mmol/mol)
Pre-diabetes	>39 and <48
Diabetes	≥48
Dyslipidaemia^64 65^	TC (mmol/l)
Borderline	≥4.40 and 5.15
Dyslipidaemia	≥5.15

BMI, body mass index; DBP, diastolic blood pressure; HbA1c, glycated haemoglobin; SBP, systolic blood pressure; TC, total cholesterol.

### Intervention

The *KaziKidz* intervention consists of a tailored, ready-made teaching material toolkit for grades 1–7 and addresses children’s risk factors for NCDs, health behaviours and psychosocial health. On the other hand, *KaziHealth* is designed as a workplace intervention targeting educators’ health and well-being through health risk assessments and personalised lifestyle coaching. The interventions have been described in detail elsewhere^30^ and all teaching materials and other project resources are freely available online.^37^

After conclusion of the *KaziBantu* RCT in 2019, all eight schools were given the freedom to conduct *KaziKidz* and *KaziHealth*. Thus, all children from grades 1–7 may have participated in *KaziKidz*, regardless of health condition. However, the implementation of *KaziKidz* and *KaziHealth* has proceeded independently and without support from the project team in all schools, under so-called «real-world» conditions. Therefore, the delivery of the programmes might have been only partially implemented. For instance, some schools might have needed to adapt *KaziKidz* to comply with COVID-19-related requirements, while other schools might have not been able to, or decided not to, continue with the intervention at all.

### Study design

This study represents an observational follow-up of the *KaziBantu* RCT and has been designed as a longitudinal study to investigate the long-term effects of both lifestyle interventions, *KaziKidz* and *KaziHealth*, on health parameters and behaviours of a cohort of high-risk children, as well as all educators originally included in the RCT. The overall effectiveness and sustainability of the programmes will be assessed using a mixed-methods approach, including quantitative and qualitative data collection methods and analyses (figure 1). Recruitment has started in March 2021. Assessments of health outcomes will be performed both for children and educators at two time points: April 2021 and September 2021, that is, 1.5 and 2 years post-RCT, to evaluate the maintenance of healthy, active lifestyles and its effect on an individual level. As part of the postintervention evaluation, the extent of *KaziKidz*’s implementation in the schools will be obtained from school representatives at both time points to be able to correlate the observed outcomes with continued participation in the original intervention. A qualitative analysis of the school headmasters’ experiences with *KaziKidz,* as well as of its incorporation into the schools’ curriculum with officials from the ECDoE, will take place 2 years post-RCT, in October 2021. Additionally, qualitative analyses will also be conducted with school educators on their experiences with, and incorporation of, *KaziHealth* into their lifestyles 2 years post-RCT, in October 2021. Further information on the adoption and acceptance of *KaziKidz* by educators and parents, and of *KaziHealth* by school headmasters’ and ECDoE officials will be obtained during October 2021.

**Figure 1 F1:**
[figure not shown]
Overview of the follow-up study design to assess the sustainability and effectiveness of *KaziKidz* and *KaziHealth*.

This postintervention sustainability assessment does not involve the evaluation of programme delivery adequacy. Similarly, the research team will not influence the effect that «real-world» conditions might have on whether, or how, the interventions are delivered in the schools. Since the studied cohort does not involve the follow-up of a control group, participants from schools refusing the implementation would serve as comparison groups for potential health and behavioural effects.

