### Longitudinal analysis

Mixed linear regression: Associations between longitudinal changes in continuous variables (eg, BMI) and individual characteristics, like sex and SES, will be assessed with random intercepts for schools and classes. Longitudinal changes in these outcomes will also be compared between the previous intervention and control schools after adjustment for personal characteristics. Moreover, changes in health parameters will be regressed against changes in PA and nutritional parameters. All analyses will be conducted, with and without adjustment, for the postintervention values of the respective outcomes. Also, potential associations between adjusted school-specific means of longitudinal changes in health parameters and the retrospectively assessed degrees of implementation of intervention measures in the respective schools will be assessed.

Mixed logistic regression: Longitudinal changes in categorical outcomes will be analysed by dichotomising polytomous outcomes. Analyses will be stratified according to the postintervention value of the dichotomised outcome, using mixed logistic regression models of the follow-up outcome with the same random effects structure and the same predictor variables, as previously described, for the mixed linear models. Additional analyses will be conducted by treating the postintervention and the two consequent FU outcomes as repeated measures.

To adjust for biases associated with missing data and/or lost to follow-up, inverse probability weighting will be used. Data imputation will be considered as an additional option if the drop-out rate is moderate (ie, <20%).

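### The design section says no control group is followed and names schools that refuse the programme as comparators, although the cohort includes the randomised control schools and the analysis section compares them

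*Protocol article*

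**What the plan says.** The Introduction describes the parent study as "implemented as a cluster randomised controlled trial (RCT) between January and October 2019". Research setting says of the KaziBantu trial: "This study is conducted in the eight schools originally selected for the". Study population reports that both interventions ran in four schools, "whereas the other four participating schools were used as controls". For children, "482 children were allocated to the intervention and 493 to the control arm". For educators, 85 of 160 took part in KaziHealth and "75 served as waiting-list controls".

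The follow-up cohort is defined from the whole trial. Of the 975 children, "544 were classified as «high risk» according to the above-mentioned definition", and all 160 educators are eligible.

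The paragraph below Figure 1 in Study design then states: "Since the studied cohort does not involve the follow-up of a control group, participants from schools refusing the implementation would serve as comparison groups". The purpose given there is to look at potential effects on health and behaviour.

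The analysis sections take a different line. Cross-sectional analysis adjusts for school type, intervention or control. Longitudinal analysis says: "Longitudinal changes in these outcomes will also be compared between the previous intervention and control schools after adjustment for personal characteristics". It also plans a school-level association between outcome change and degree of implementation.

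**The concern.** The first objective is long-term effectiveness. The article offers two contrasts for it, and the design section denies that the groups needed for one of them exist.

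The contrasts mean different things. Former intervention versus former control schools starts from randomisation. Refusing versus implementing schools starts from a decision that each school made after the trial. The Intervention section says some schools may have been unable to continue, or chose not to, and that some may have had to adapt to COVID-19 requirements. The Discussion adds that poorer schools were least able to catch up. Such reasons plausibly affect child and educator health directly, so a difference between these groups need not reflect the programme.

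The named comparator is also loosely fixed. Refusal is not defined, although the Intervention section describes partial, adapted and absent delivery. The implementation questionnaire covers KaziKidz only, while KaziHealth implementation is explored in focus groups. For educators, therefore, no questionnaire measure is described that would sort schools into the two groups.

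A team following the design section would rest its effectiveness claim on the weaker contrast.

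**Working it through.** **1. The article's own totals (Study population).**
- Children: 482 + 493 = 975, as stated.
- Eligible children: 544 − 183 = 361, as stated.
- Educators: 85 + 75 = 160, as stated.

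**2. Are former controls in the cohort?**
- High-risk children: at most 482 of the 544 can come from the intervention arm, so at least 544 − 482 = 62 were control children.
- This bound does not carry over to the 361. The 183 who left primary school exceed 62, and the split by arm is not given for the 361 eligible or the 240 enrolled. That former control children remain rests on the follow-up being in all eight schools and on the planned arm comparison.
- Enrolled educators: at most 85 of the 105 can be intervention educators, so at least 105 − 85 = 20 are former waiting-list controls. This bound applies directly to people already enrolled.

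**3. The statements side by side.**
- Study design: no control group is followed; refusing schools are the comparison.
- Research setting and Study population: all eight schools are followed, four of which were controls.
- Cross-sectional and Longitudinal analysis: school type is an adjustment variable, and change is compared between the former arms.

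If the first statement were literally true, the arm terms in the third could not be estimated.

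**4. What the refusing-school comparator could deliver.** The number of refusing schools, k, is not given, so the range 0 to 8 is shown. Taking equal between-school variance and a two-group split (both assumptions), the between-school standard error relative to four against four is √(1/k + 1/(8−k)) ÷ √(1/4 + 1/4). The smallest exact school-level p-value, doubling the one-sided tail, is 2/C(8,k).

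| Split of schools | SE ratio | Smallest exact p |
|---|---|---|
| 4 vs 4 | 1.00 | 2/70 = 0.029 |
| 3 vs 5 | 1.03 | 2/56 = 0.036 |
| 2 vs 6 | 1.15 | 2/28 = 0.071 |
| 1 vs 7 | 1.51 | 2/8 = 0.25 |
| 0 or 8 refusing | no comparison | – |

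**5. Bias.** Any underlying difference in outcome change between schools able and unable to continue enters this contrast one for one. The article gives no figure for it. If it were 0.1 to 0.3 SD (an assumption with no source in the document), the apparent effect would be shifted by 0.1 to 0.3 SD.

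**6. How intact is the arm contrast?** Enrolment so far is 240/361 = 66% of eligible children and 105/160 = 66% of educators. Child risk status comes from data dated July 2019, inside a trial that ran from January to October 2019, so it is unclear whether selection preceded exposure. The 183 children who left primary school are excluded.

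**The case against.** A reader might infer that the plan has replaced a randomised comparison with a self-selected one. The document does not support that: Longitudinal analysis explicitly keeps the comparison of former intervention and control schools, and Cross-sectional analysis carries school type as an adjustment.

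There is also a charitable reading of the disputed sentence. After 2019 all eight schools were free to run both programmes, so no group was held unexposed. The sentence follows text on real-world delivery, and Study design says outcomes are to be related to continued participation. On that reading, non-implementing schools are the natural reference for continued implementation, and the two contrasts answer different questions. This is plausible, but the sentence does not say it. It denies follow-up of a control group outright.

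Nor is the refusing-school contrast open to every bias. Those schools are concurrent, their children met the same risk rule, and all eight schools are in the same poverty quintile, so calendar time, growth and regression to the mean are largely shared. Its particular weakness is selection, which the shared quintile limits but does not remove.

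The arm contrast should not be oversold either, given step 6 of the working, the small number of clusters and the freedom of control schools to adopt the programme.

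Finally, a full ranking of analyses is often left to a longer document. That is fair, but it does not excuse a design statement that contradicts the analysis in the same article.

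**Conclusion.** The concern holds as an internal contradiction. Study design denies a control group that the cohort contains and the analysis uses, and puts in its place a comparator chosen by the schools after randomisation, possibly confounded and possibly empty. The contradiction rests only on the article's own text and counts: at least 62 of the 544 high-risk children and at least 20 of the 105 enrolled educators were controls.

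The cost to precision depends on an unknown number of refusing schools. It ranges from negligible at three against five to a standard error 1.51 times as large at one against seven, with no comparison at all at zero or eight. The size of any bias cannot be derived from the document.

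Two stronger conclusions are not supported. The randomised comparison has not been abandoned, and the arm counts are not wrong. Study population already gives them correctly; only the looser wording nearby blurs them. The arm contrast is preferable because it alone starts from randomisation, not because it is fully protected by it.

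**What to change.** - Reword the sentence below Figure 1 to say that former control schools are followed up but were free to adopt the programmes after the 2019 trial.
- Make former intervention versus former control schools, as randomised, the main effectiveness comparison for children and educators. Describe it as 'programme in 2019 plus optional continuation' versus 'optional uptake after 2019'.
- Keep implementing versus non-implementing schools, or degree of implementation, as an observational and exploratory analysis adjusted for original arm.
- Align the phrases that put all 975 children in KaziKidz and all 160 educators in KaziHealth (Abstract and Study population) with the arm counts already given: 482/493 and 85/75.
- State the limits of the arm contrast: possible dilution by uptake in control schools, high-risk selection on July 2019 data, exclusion of the 183 children who left primary school, and about 66% enrolment so far.

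The cost is wording only, with no new data collection. The price in interpretation is that the main contrast concerns earlier randomised exposure and may understate the effect of continued delivery.
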